**Baseline covariates**								
	**Demographics**							
		Questionnaire	✓					
	**Psychological distress**							
		SRQ-20^a^ [44]	✓		✓		✓	
	**Depression**							
		PHQ-9^b^ [43]	✓		✓		✓	
		WMH CIDI^c^ [46]	✓					
	**HIV stigma**							
		Berger Stigma Scale [55]	✓					
	**Social support**							
		Social Provision Scale [56]	✓					
	**Food insecurity**							
		Household Food Insecurity Access Scale [57]	✓					
	**Disability**							
		WHO^d^ Disability Assessment Schedule [54]	✓		✓		✓	
	**Substance abuse**							
		CRAFFT^e^ Scale [58]	✓					
	**Clinical data**							
		CD4+^f^ count, HIV viral load, ART^g^ adherence	✓		✓		✓	
**Primary outcomes**								
	**Engagement**							
		Percentage of sessions attended			✓			
	**Satisfaction**							
		CSQ-8^h^ [51], FGD^i^			✓			
	**Feasibility, acceptability, appropriateness**							
		Weiner’s FIM^j^, AIM^k^, IAM^l^ surveys [52]; enrollment rate; mobile phone or data needs; game play metrics; FGD			✓			
**Secondary outcomes**								
	**ART adherence**							
		Percentage of pharmacy refill	✓		✓		✓	
	**HIV viral load**				✓		✓	

^a^SRQ-20: Self-Reporting Questionnaire-20.

^b^PHQ-9: 9-item Patient Health Questionnaire.

^c^WMH CIDI: World Mental Health Composite International Diagnostic Interview.

^d^WHO: World Health Organization.

^e^CRAFFT: Car, Relax, Alone, Forget, Family/Friends, and Trouble Questionnaire.

^f^CD4+: cluster of differentiation 4+ T-lymphocyte cell.

^g^ART: antiretroviral therapy.

^h^CSQ-8: Client Satisfaction Questionnaire.

^i^FGD: focus group discussion.

^j^FIM: Feasibility of Intervention Measure.

^k^AIM: Acceptability of Intervention Measure.

^l^IAM: Intervention Appropriateness Measure.

#### Implementor Quantitative Data Collection

We will administer pre- and posttest knowledge assessments after initial training (focusing on screening, identification, and treatment for depression and components of PST). We will also conduct a baseline readiness assessment, including Rohrbach’s readiness tool and the Organizational Readiness for Implementing Change tool, and assess pre-implementation feasibility, acceptability, and appropriateness from health facility leaders (n=2), the HIV clinic providers (n=4), and HIV counselors (n=4-5) [59,60]. At 3 months, we will administer an assessment of implementation outcomes to this group, which will include Weiner’s Intervention Appropriateness Measure, FIM, and AIM [52]. In addition, the scalability of the intervention will be assessed using the Intervention Scalability Assessment Tool (Table 3) [61].

**Table 3 table3:** Implementer data collection.

Implementation outcome	Measure	Baseline	3 months	6 months
Workshop training assessments	Pre- or posttest, evaluation form	✓		
Readiness	Rohrbach and ORIC^a^ tools [58,59], FGD^b^	✓	✓	
Patient engagement	FGD		✓	
Feasibility	Weiner’s FIM^c^ [51], FGD	✓	✓	
Acceptability	Weiner’s AIM^d^ [51], FGD	✓	✓	
Appropriateness	Weiner’s IAM^e^ [51], FGD	✓	✓	
Fidelity	Direct observation	Ongoing	Ongoing	Ongoing
Scalability	Intervention Scalability Assessment Tool [60]		✓	

^a^ORIC: Organizational Readiness for Implementing Change.

^b^FGD: focus group discussion.

^c^FIM: Feasibility of Intervention Measure.

^d^AIM: Acceptability of Intervention Measure.

^e^IAM: Intervention Appropriateness Measure.

### Qualitative Data Collection

#### Participant Qualitative Data Collection

FGDs will be conducted with study participants (n=20) at the study end. Our FGD guide was developed using the CFIR framework and focused on determinants of key implementation outcomes (feasibility, acceptability, satisfaction, and engagement) of our patient-facing strategies and environment [36,62]. We will examine outer setting factors, such as IT infrastructure, to enable digital game use, community-level stigma, and sociocultural norms influencing mental health and HIV care. Inner setting constructs will explore participants’ perceptions of the clinic environment and its support for mental health services. Characteristics of individuals will include participants’ knowledge, beliefs, and self-efficacy related to using the digital game and engaging in PST. Intervention characteristics will be examined through perceptions of the game’s relevance, quality, and usability and the coherence between the game content and PST sessions. Finally, implementation process factors, such as clarity of instructions, support received, and game-clinic integration, will be assessed to understand what facilitated or hindered engagement. The full guide can be found in Multimedia Appendix 1. These qualitative insights will inform the contextual appropriateness and potential scalability of the intervention.

#### Implementer Qualitative Data Collection

We will conduct 2 FGDs with health facility leaders (n=2), HIV clinic providers (n=4), and HIV counselors (n=4-5), once during pre-implementation to assess knowledge and attitudes about mental health, PST, and readiness for the intervention, and again at the study end to assess implementation outcomes and their determinants. As with the participants, the CFIR will guide our assessment of implementation outcome determinants, appropriateness and feasibility of implementing this strategy in Nigeria (outer setting), the clinic’s culture and attitudes toward mental health screening and treatment, internal capacity to support mHealth-based interventions, impacts of the intervention on other services (inner setting), knowledge and beliefs about the intervention, confidence in implementor’s abilities to administer the intervention and integrate the game-based strategy into the intervention (provider characteristics), effectiveness of provider training, effectiveness of integration of the strategy into clinic workflow, facilitators and barriers to intervention fidelity (process of implementation), and complexity and quality of the intervention and implementation strategies (intervention characteristics), challenges, as well as contextual factors influencing acceptability and satisfaction with the intervention [36,62]. The full guide can be found in Multimedia Appendix 2.

### Sample Size and Power Considerations

With a total sample size of 80 participants (40 per study arm), the study will have approximately 80% power to detect a difference between the intervention and control groups equivalent to 0.635 SDs in the outcome measure using a 2-sided *t* test with a significance level of .05.

#### Engagement in the Intervention

Using prior data from a study on PST for depression and common mental disorders among adults in Zimbabwe in which the SD for the number of sessions attended was 18.5%, we anticipate having 80% power to detect a difference of 11.7% in the mean proportion of sessions attended between the study arms [24]. If the SD in our study population is as low as 10% or as high as 25%, then we will have approximately 80% power to detect mean differences in the proportion of sessions attended of 6.3% and 15.8%, respectively. If up to 20% (16/80) of participants are lost to follow-up (LTFU), then we anticipate having 80% power to detect a difference of 13.2% in the mean proportion of sessions attended between the study arms.

#### Satisfaction With the Intervention

While there are no preliminary data in similar populations, in diverse populations receiving PST, the SD of the CSQ-8 (scores range from 8 to 32) was 4.78-4.95 [63,64]. Assuming SDs of 4.5, 4.75, and 5.0 in the CSQ-8 scores and no LTFU, we anticipate having 80% power to detect differences of 2.9, 3.0, and 3.2, respectively, in the mean scores between study arms. With 20% (16/80) LTFU, these estimated detectable differences are 3.2, 3.4, and 3.6, respectively. While we will not be powered to detect differences in our secondary clinical outcomes in this pilot RCT, we believe the value of this intervention approach may not necessarily come from changing PST efficacy but from improving adoption and engagement for young people living with HIV with the intervention, thus improving its overall effectiveness or so-called mosaic effectiveness [65].

#### Retention

To promote retention and minimize LTFU, we will use established clinic strategies including phone reminders for appointments and targeted outreach by clinic or study staff for missed visits. To reduce participation burden, only 3 PST sessions will be required to be in person, others can be delivered via mobile phone (per participant preference), and participants will receive travel reimbursement and refreshments for the face-to-face sessions and outcome assessments. Participants who elect to discontinue from the study will be asked to complete an exit visit, which will include the assessments outlined in Table 2.

### Data Analysis

#### Overview

Primary outcomes include (1) engagement in the intervention defined as the percentage of recommended PST sessions attended, (2) satisfaction with the intervention using the CSQ-8, (3) feasibility, and (4) acceptability (from the patient perspective; Table 2). These outcomes will be collected throughout the course of the study through engagement with the app and participation in PST sessions. Exceptions include the CSQ-8, FIM, and AIM, which will be administered at 3 months, and the fidelity checklist, which will be applied to 2 separate sessions during the study.

Our secondary outcomes include remission of depression, level of mental distress, disability, ART adherence, and HIV viral suppression (Table 2). These outcomes will be assessed at 3 and 6 months (viral suppression will be assessed once between 3 and 6 months).

#### Quantitative Data Analysis

Engagement and satisfaction scores (primary outcomes) and ART adherence (secondary outcome) will be compared between study arms using a Wilcoxon rank sum test to avoid making distributional assumptions. Additional secondary outcomes (remission of depression and psychological distress and viral suppression) will also be compared using chi-square tests. We will compare primary and secondary outcomes between study arms using semiparametric cumulative probability models. Because of the relatively small sample size, baseline covariates will be included using a propensity score to account for any covariate imbalance between the treatment arms. Missing covariate data, if any, will be multiply imputed with 20 imputation replications using chained equations. Primary analyses will be intention-to-treat analyses; we will also perform secondary, as-treated analyses. Persons who are out of care will be assumed to have been nonadherent over the period for which they were out of care, and intervention engagement over these gaps will be assigned the value 0. Secondary analyses will exclude person-time when individuals are not in care. Descriptive statistics will be used to summarize the ordinal responses obtained from FIM and AIM surveys in addition to programmatic and game log data measuring other features of feasibility and acceptability. We will assess other factors associated with the study primary and secondary outcomes, in addition to potential confounders and mediators of the relationship between the intervention and outcome including baseline sex, cluster of differentiation 4+ T-lymphocyte cell count, age, marital status, psychological distress, HIV stigma, social support, food insecurity, quality of life, and substance abuse [43,44,55,57,66-70].

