**Methods:**

We will conduct a pilot hybrid implementation-effectiveness randomized controlled trial with 80 young people living with HIV (aged 16-24 years) in Nigeria with depression (9-item Patient Health Questionnaire [PHQ-9] ≥9) over 3 months. Participants will be randomized to receive PST with or without Change My Story. All participants will engage in weekly PST sessions for 6 weeks delivered by trained nonspecialists (clinic HIV adherence counselors). At 6 and 10-12 weeks, scores on PHQ-9 will determine the frequency of PST sessions during the remaining intervention period. Primary implementation outcomes, including engagement, satisfaction, feasibility, acceptability, and appropriateness from the participant perspective, will be assessed using validated scales, programmatic data, and focus group discussions at 3 months. Secondary clinical outcomes will assess changes in depressive symptoms, psychological distress, functional disability, antiretroviral therapy adherence, and HIV viral suppression at 3 and 6 months. Implementation outcomes (all but engagement and satisfaction) will be assessed through validated scales and focus group discussions from the implementer perspective at baseline and 6 months.

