Secondary outcomes are clinical outcomes (remission of depression or psychological distress, ART adherence, and viral suppression). Specifically, remission will be defined by a reduction in PHQ-9 from baseline to follow-up (PHQ-9 score <6) [43,44]. Functioning across 6 domains will be measured via the WHO Disability Assessment Schedule [54]. HIV outcomes, including ART adherence and viral suppression, will be, respectively, measured via pharmacy refills and laboratory values (HIV RNA <200 copies per milliliter) at baseline and 3 to 6 months after intervention completion. Laboratories will be drawn for this assessment if participants do not have a routine clinical viral load obtained within this window.

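### Depression and distress are named for analysis mainly as yes/no remission; no sentence makes the PHQ-9 or SRQ-20 score the analysed variable, and distress remission has no definition

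*Protocol article*

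**What the plan says.** All references are to the protocol article.

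- **Abstract, Methods:** "Secondary clinical outcomes will assess changes in depressive symptoms, psychological distress, functional disability", among others, at 3 and 6 months. The abstract's Results paragraph, however, states the hypothesis as greater depression remission.
- **Choice of Comparators:** the hypothesis on effectiveness concerns the PHQ-9 score.
- **Outcome Assessment:** the clinical outcomes are remission of depression or distress, ART adherence and viral suppression; "remission will be defined by a reduction in PHQ-9 from baseline to follow-up (PHQ-9 score <6"). No equivalent rule is given for the SRQ-20.
- **Data Analysis, Overview:** "Our secondary outcomes include remission of depression, level of mental distress, disability, ART adherence, and HIV viral suppression", and "These outcomes will be assessed at 3 and 6 months". Here depression is remission, but distress is a level.
- **Quantitative Data Analysis:** "Additional secondary outcomes (remission of depression and psychological distress and viral suppression) will also be compared using chi-square tests". Then: "We will compare primary and secondary outcomes between study arms using semiparametric cumulative probability models". On adjustment: "baseline covariates will be included using a propensity score to account for any covariate imbalance between the treatment arms".
- **Table 2:** PHQ-9 and SRQ-20 are both ticked at baseline, 3 months and 6 months.
- **Satisfaction With the Intervention** (under sample size): the trial is acknowledged not to be powered for the clinical outcomes.

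**The concern.** Three things are at issue.

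1. **Lost information.** Cutting a multi-point score at one value treats a participant who falls from 16 to 6 the same as one who stays at 16. In a pilot meant to give preliminary effect data for a larger trial, that is an avoidable loss: the scores are collected anyway and the planned model can use them.
2. **Unclear variable.** Depression is a change, a score or a remission depending on the section, and distress is a level or a remission. A reader cannot tell which result will carry the statement on preliminary effectiveness. The trial is open to participants and implementers and already enrolling, so this should be settled before results are seen.
3. **An outcome that cannot be computed as written.** Everyone enters with PHQ-9 of at least 9, so a follow-up value below 6 is a real fall. Entry sets no SRQ-20 level, so the same logic does not carry over to distress.

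**Working it through.** **Step 1: the plan's own figure.** Inputs from Sample Size and Power Considerations: 40 per arm, two-sided t test, alpha .05, difference 0.635 SD. The noncentrality is 0.635 × √(40/2) = 2.84 with 78 degrees of freedom, giving power 0.801. The stated value of about 80% is reproduced.

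**Step 2: the cost of cutting the score.** The article gives no PHQ-9 SD and no expected remission rate. Assumptions: a normal score with equal SD in both arms, a shift of d SD, and control remission p1 from 30% to 70%. Then:

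- remission in the game arm: p2 = Φ(Φ⁻¹(p1) + d)
- chi-square power: Φ{[p2 − p1 − 1.96·√(2·p̄(1−p̄)/n)] / √[(p1(1−p1) + p2(1−p2))/n]}, with p̄ the mean of p1 and p2

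Example with p1 = 0.50, d = 0.635, n = 40: p2 = 0.737 and p2 − p1 = 0.2373. The null term is 1.96 × 0.1086 = 0.2129 and the denominator is 0.1053. Power = Φ(0.0244/0.1053) = Φ(0.232) = 0.59.

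All cases at 40 per arm:

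| Control remission | p2 at 0.635 SD | Chi-square power at 0.635 SD | p2 at 0.5 SD | Chi-square power at 0.5 SD |
|---|---|---|---|---|
| 30% | 0.544 | 0.602 | 0.490 | 0.411 |
| 40% | 0.649 | 0.608 | 0.597 | 0.421 |
| 50% | 0.737 | 0.592 | 0.691 | 0.413 |
| 60% | 0.813 | 0.553 | 0.774 | 0.389 |
| 70% | 0.877 | 0.490 | 0.847 | 0.347 |
| **t test on the score** | | **0.801** | | **0.598** |

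With the article's 20% loss (32 per arm), the score gives 0.71 against 0.41 to 0.51 at 0.635 SD, and 0.50 against 0.29 to 0.35 at 0.5 SD. For 80% power at 0.635 SD the binary comparison needs 63 to 83 per arm, against 39 for the score by the normal approximation: 63/39 = 1.6 to 83/39 = 2.1 times as many.

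**Step 3: check on whole-number scores.** Simulated PHQ-9 values (assumed control mean 6, SD 4, rounded and bounded, cut below 6; 4,000 replicates), with a rank test standing in for an unadjusted cumulative probability model on the score. At 0.635 SD: 0.77 against 0.63 for chi-square. At 0.5 SD: 0.57 against 0.44. The gap is about 14 points here, against 19 to 31 points in Step 2 at 0.635 SD. The direction agrees; the size depends on the assumptions.

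**Step 4: baseline adjustment, a separate gain.** Adjusting the score for its baseline value divides the residual SD by 1/√(1−r²). At 0.5 SD and 40 per arm, power rises from 0.60 to 0.64 with r = 0.3 and to 0.72 with r = 0.5. Both correlations are assumed, and this gain is not part of the comparison in Step 2.

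**Step 5: does the model sentence recover the loss?** Only if the score is the response. With two categories a cumulative probability model has one cut point and is a binary regression. For depression, Outcome Assessment, Overview and Quantitative Data Analysis all name remission.

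**The case against.** A reader might infer that depression and distress are compared by chi-square alone and that the scores are thrown away. The text does not support that. The chi-square sentence says these outcomes will also be compared that way, and the next sentence applies cumulative probability models to primary and secondary outcomes. Overview lists distress as a level. Disability, also a secondary outcome, has no other named test, so the model sentence presumably covers at least one score. The passages are compatible with score analyses being intended.

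A reader might also infer that non-distressed participants will be counted as remitted. That would need an SRQ-20 rule the article does not give; an unseen analysis plan could restrict the outcome to those above a threshold at baseline.

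It is also fair that PHQ-9 below 6 is the trial's own remission threshold in stepped care, is a stated hypothesis and is easy to interpret, and that the power figures rest on assumed inputs. Baseline PHQ-9 is restricted in range by the entry rule, so r = 0.5 may be optimistic. Table 2 puts PHQ-9 among the baseline covariates, so it may already enter the propensity score.

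What does not fall away: the article does more than stay silent. It names the outcome variables, names them differently from section to section, and where it ties depression to an analysis it names remission. A chi-square test of distress needs a binary variable, which conflicts with the level listed in Overview.

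**Conclusion.** The point holds in this form: depression is specified for analysis as remission, distress is specified as both remission and level, no sentence makes either score the analysed variable, and SRQ-20 remission is undefined. The documents do not show that chi-square is the sole analysis or that scores will be discarded.

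If the analyses do stay binary, the loss at 40 per arm is material: about 80% against 49% to 61% power at 0.635 SD, and about 60% against 35% to 42% at 0.5 SD. This assumes a normal score, equal SDs and control remission of 30% to 70%, and the whole-number simulation gives a smaller gap of about 14 points. If the models are fitted to the scores, most of the loss disappears and only the naming conflict and the undefined distress outcome remain.

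Severity is low to moderate. These are secondary outcomes in a pilot that says it is not powered for them. That admission does not justify giving up information already collected, but it limits what is at stake.

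**What to change.** 1. State that the cumulative probability models for depression and distress use the PHQ-9 and SRQ-20 scores at 3 and 6 months, with the matching baseline score and the two stratification factors (age category and mode of HIV transmission) as covariates.
2. Keep PHQ-9 below 6, with its chi-square test, as a supporting result.
3. Replace remission of psychological distress with the SRQ-20 score.
4. Reconcile the abstract, Choice of Comparators, Outcome Assessment, Overview and Quantitative Data Analysis so that each outcome has one name and one form.

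The cost is wording in the protocol and analysis plan: the data and the model are already planned. The downside is that a score difference is less directly clinical than a remission rate, but remission is still reported.

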### Randomization

Participants with a PHQ-9 score ≥9 will be randomized 1:1 in a parallel group design by the study statistician to study arm 1, PST alone, or study arm 2, PST with Change My Story. Randomization will be stratified on 2 key baseline variables: age category (16-19 vs 20-24 years) and HIV mode of transmission (perinatal vs nonperinatal). Younger people living with HIV in LMICs may have more limited access to technology, which may impact the feasibility of the mHealth platform [47]. Perinatally and nonperinatally infected young people living with HIV often differ in psychosocial contexts and stigma experiences, which may influence both their engagement with the intervention and mental health outcomes [48]. The random allocation sequence will be generated centrally by the study statistician and implemented using sequentially numbered, opaque, sealed envelopes to ensure allocation concealment until the point of assignment.

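### The simple tests leave out the two randomization strata, and the model's propensity score should give way to direct adjustment for those strata and for baseline values where they exist

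*Protocol article*

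**What the plan says.** The Randomization section states: "Randomization will be stratified on 2 key baseline variables: age category (16-19 vs 20-24 years) and HIV mode of transmission". It justifies the second factor by saying that perinatally and nonperinatally infected participants may differ in engagement and in mental health outcomes.

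The Quantitative Data Analysis section then fixes three things.

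- Engagement, satisfaction and ART adherence "will be compared between study arms using a Wilcoxon rank sum test to avoid making distributional assumptions". Remission and viral suppression get chi-square tests. Neither test is described as stratified or adjusted.
- Primary and secondary outcomes are also compared with semiparametric cumulative probability models. Citing the small sample, the section says that "baseline covariates will be included using a propensity score to account for any covariate imbalance between the treatment arms". It does not list the covariates in the score.
- A later, separate sentence names ten variables to be examined as correlates, confounders or mediators. Age is among them. Mode of transmission is not, and it appears nowhere else in Data Analysis.

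Table 2 has a block of baseline covariates that includes PHQ-9, SRQ-20, the WHO disability scale, viral load and ART adherence. Engagement and the CSQ-8 are recorded at 3 months only.

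**The concern.** When randomization is stratified on prognostic factors, the arms are balanced on them by design. The treatment estimate becomes more precise, but an analysis that leaves the factors out does not see this: its standard error still carries the between-stratum variance, so the test is conservative. The protocol itself gives a reason to think one stratum is prognostic for a primary outcome.

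The propensity score does not repair this. In a randomized trial there is no systematic confounding for it to remove. It is built to predict arm, and chance imbalance aside it explains little of the outcome. Entered as a covariate it corrects the point estimate for imbalance, but leaves the residual variance, and so the default standard error, nearly unchanged. At stake is power in a trial of 80, where a few direct terms would recover it from data already being collected.

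**Working it through.** **Inputs from the protocol article (Sample Size and Power Considerations).** "With a total sample size of 80 participants (40 per study arm"), 80% power for a difference "equivalent to 0.635 SDs in the outcome measure using a 2-sided" t test, "with a significance level of .05". For engagement, "the SD for the number of sessions attended was 18.5"%.

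**Assumptions, not in the documents.** R² of the strata with the outcome: 0 to 0.2. R² of a baseline value: 0, 0.25 or 0.4. Seven further non-prognostic covariates in the score. Permuted blocks of 4. Score entered as a covariate with model-based standard errors.

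**Step 1: the plan's own figures reproduce.** In SD units, SE = √(2/40) = 0.2236, and 0.635/0.2236 = 2.840. The normal approximation gives power Φ(2.840 − 1.960) = 81.1%; the noncentral t gives 80.1%. The detectable difference is 0.634 SD, and 0.634 × 18.5 = 11.73 points (stated 11.7). With 32 per arm it is 13.16 points (stated 13.2). The CSQ-8 figures also reproduce.

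**Step 2: closed form for direct adjustment.** SE = 0.2236 × √(1 − R²).

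- R² = 0.10: SE 0.2121, power Φ(0.635/0.2121 − 1.960) = Φ(1.034) = 84.9%
- R² = 0.20: SE 0.2000, power Φ(1.215) = 88.8%
- R² = 0.35 (strata 0.1 + baseline 0.25): SE 0.1803, power Φ(1.562) = 94.1%

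An unadjusted analysis after stratified randomization reports 0.2236 although the true SE is the smaller value. With strata R² of 0.1 or 0.2 its SE is too wide by a factor 1/√0.9 = 1.054 or 1/√0.8 = 1.118.

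**Step 3: simulation, n = 80.** Power is at 0.635 SD. The SE ratio is mean model SE over true SE for the propensity-score analysis with no effect. "Direct" means terms for strata and, where prognostic, the baseline value.

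| Model | R² strata; baseline | Unadjusted | Propensity score | Direct | SE ratio, score | Type I, score |
|---|---|---|---|---|---|---|
| Linear (3000 runs) | 0.1; 0 | 80.8% | 75.5% | 83.6% | 1.04 | 4.3% |
| Linear | 0.2; 0 | 82.8% | 78.9% | 88.2% | 1.11 | 3.4% |
| Linear | 0.1; 0.25 | 82.3% | 81.6% | 93.5% | 1.24 | 1.6% |
| Linear | 0.1; 0.4 | 80.3% | 83.6% | 97.3% | 1.34 | 0.8% |
| Cumulative (1500 runs) | 0; 0 | 75.7% | 73.2% | 76.3% | 0.97 | 5.4% |
| Cumulative | 0.1; 0 | 78.8% | 73.9% | 83.3% | 1.04 | 4.3% |
| Cumulative | 0.2; 0 | 80.3% | 76.1% | 87.9% | 1.10 | 3.3% |
| Cumulative | 0.1; 0.25 | 79.1% | 78.7% | 92.4% | 1.14 | 2.8% |

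Across the prognostic rows, direct minus propensity score runs from 83.6 − 75.5 = 8.1 to 97.3 − 83.6 = 13.7 points. In the linear model with nothing prognostic, the score gave 75.8% against 79.8% unadjusted, with SE ratio 1.00.

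**Step 4: where the loss comes from.** Entering every covariate of the score directly gave 78.8%, 85.5%, 91.4% and 95.4% in the four linear rows. In the first row, 83.6 − 78.8 = 4.8 points go to the non-prognostic covariates and 78.8 − 75.5 = 3.3 to the unexplained variance. In the third, the split is 2.1 and 9.8. The true SE of the score-adjusted estimate matches that of full direct adjustment (0.2245 and 0.2245 in row 1; 0.1900 and 0.1899 in row 3). The estimate is therefore sound, and its reported SE is what is wrong.

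**Step 5: does the unknown content of the score matter?** With strata and baseline left out of the score, linear power was 76.3%, 79.1%, 78.8% and 76.5%, also well below direct adjustment.

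**Step 6: Wilcoxon without strata.** Type I error was 4.0% and 2.9% at strata R² 0.1 and 0.2. Power was 77.9% and 80.8%, against 83.6% and 88.2% for direct adjustment. Part of that gap belongs to the rank test itself, since the unadjusted t test had 80.8% and 82.8%.

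**The case against.** The article condenses a fuller plan, and the covariates in the score are the kind of detail such a plan would hold. Several stronger readings fail for that and other reasons.

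- *The model ignores the strata and baseline PHQ-9.* A reader might infer this from the list of ten variables, but that list belongs to a different sentence and is not said to define the score. Table 2 counts baseline PHQ-9 among the baseline covariates. Omission is established only for the Wilcoxon and chi-square tests.
- *The propensity score is worse than no adjustment.* In the table it ranges from 5.3 points below the unadjusted analysis (75.5 against 80.8) to 3.3 above (83.6 against 80.3). Only the shortfall against direct adjustment is consistent.
- *The primary outcomes lose the full amount.* Engagement and CSQ-8 have no baseline value, so only the strata rows describe them. The larger figures concern secondary outcomes, for which the article already says it lacks power.
- *The tests are invalid.* With prognostic covariates the unstratified and score-adjusted tests reject too seldom, so they do not generate false positives.
- *Remission should yield to the PHQ-9 score.* The plan says "remission will be defined by a reduction in PHQ-9 from baseline to follow-up (PHQ-9 score <6"). Preferring the full scale is a debatable choice. The Abstract also promises changes in depressive symptoms, and the cumulative probability model can take a score.

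What stands of the objection is that prognostic strength is assumed, and that a robust or bootstrap variance could correct the standard error. The article specifies no variance estimator.

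**Conclusion.** The concern holds in limited form. The simple tests leave out both randomization strata, and mode of transmission is named nowhere in the analysis although the design section expects it to matter. The propensity score is an inefficient substitute for direct adjustment, and small sample size does not argue for it.

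With strata R² of 0.1-0.2, default standard errors are about 4-11% too wide. With a baseline value at R² 0.25 added, they are about 14-24% too wide. Type I error then falls below 5%, and power is about 8-14 points lower than with direct adjustment. With no prognostic covariate, standard errors are correct and the loss is about 4 points in the linear model (2.5 in the cumulative model, 75.7 − 73.2). All of this rests on the assumed R² values, on the seven non-prognostic covariates assumed in the score, and on model-based standard errors. The cost is sensitivity, not validity, and the sample-size statement needs no correction.

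**What to change.** In the planned cumulative probability model, replace the propensity score with direct terms for age category and mode of transmission for every outcome. For secondary outcomes with a baseline measurement (PHQ-9, SRQ-20, disability, refill adherence, viral load), add that outcome's own baseline value. For engagement and CSQ-8 only the two strata apply. If the simple tests are kept, use the stratified forms: van Elteren in place of Wilcoxon, and Cochran-Mantel-Haenszel in place of chi-square.

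This is a wording change that needs no new data. By the article's timeline follow-up runs to June 2026, so it can be fixed before analysis. There are two costs. Effects become conditional on a few baseline variables, which slightly changes their interpretation. And the directly adjusted cumulative model rejected 5.7% to 6.5% of the time with no effect, where Monte Carlo error is √(0.05 × 0.95/1500) = 0.6 points. Part of its power advantage may reflect this, and its small-sample test should be checked, for example against a permutation test within strata. The directly adjusted linear model stayed at 4.9% to 5.4%.
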